#### 12.2.15 Check Cervical intraepithelial neoplasia (CIN 1) progress

Observe for 8 weeks after completion of the Investigational Product from visit 2 (0 weeks) to visit 3 (4 weeks ± 5 days). At the final visit of the Visit 5 (12 weeks ± 5 days), an effective evaluation test of the cervical dysplasia including Colposcopic Biopsy is performed. If the progression is on the Colposcopic Biopsy, the standardized treatment method and terminates the clinical trial of the patient.

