### 15.1.2 Secondary Validity Variables

Compared to baseline (within -4 weeks) before drug administration Reid Colposcopic Index at 12 weeks after drug administration

Compared to baseline (within -4 weeks) before drug administration Pap smear test results at 12 weeks after drug administration

Comparison of HPV DNA chip test results at 12 weeks after drug administration compared to Baseline (within -4 weeks) before drug administration HPV HC Ⅱ assay results at 12 weeks after drug administration compared to baseline (within -4 weeks)

Comparison of results of NK cell activity at 4, 8 and 12 weeks after drug administration compared to baseline (0 week) before drug administration

(MHC class II) CD8, CD56 population at 4 weeks, 8 weeks, and 12 weeks after administration of drug compared to baseline (0 week) before drug administration.

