#### 15.2.2 The secondary efficacy end point

1) Comparison of Reid Colposcopic Index after administration of drug

Reid Colposcopic Index is a grading system that classifies and scales various findings of CIN lesions according to their characteristics. The score is scored from 0 to 8, and the grading according to the score is determined as follows.

0-2: Likely to be CIN I

3-4: Overlapping lesion - likely to be CIN I or CIN II

5-8: Likely to be CIN II

2) Comparison of Pap smear test results after administration

Cervical cytology was performed using the two-slide technique, using a cytobrush of the uterus and an ectopic cytobrush. The cervical cytology was based on the 2001 Cervical Cytologic Diagnoses. The readings are read in six steps: negative, ASC-US, ASC-H, LSIL, HSIL, and invasive cancer (cervical carcinoma).

3) Comparison of HPV DNA chip test results after administration of drug

Cervical cytology is performed using a specimen collected from uterine and ectopic cytobrush. To confirm the correlation between tumor epithelial cells and HPV infection and virus type. HPV types 16 and 18, 31, 33, 35, 39, 45, 51 and 52 are recorded for positive and negative HPV.

4) Comparison of HPV HC Ⅱ assay results after drug administration

Cervical cytology is performed using a specimen collected from uterine and ectopic cytobrush. It is an examination that is performed as one of the methods to predict the severity of cervical intraepithelial neoplasia. The test result is classified as positive or negative based on the light unit of the sample. If the result is positive, it is recorded as Low, Intermediate, High.

5) Comparison of results of NK cell activity after administration of drug compared to drug administration

Blood is collected from visit 2 and visit 3, visit 4, visit 5, and it is evaluated according to the measurement method of 12.2.8 1).

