#### 15.3.3 Missing value processing method

In the analysis of validation variables, LOCF (Last Observed Carried Forward) method is applied to replace missing values, and safety evaluation parameters are analyzed without substitution if there is a mistake.

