### 15.3.5 Analysis of secondary primary efficacy endpoints

Secondary efficacy variable 1: Reid Colposcopic Index

0-2 Score: Likely to be CIN I

3-4 Score: Overlapping lesion - likely to be CIN I or CIN II

5-8 Score: Likely to be CIN II

The comparison between the baseline scores and the difference of the scores after 12 weeks will be confirmed through the t-test or the Wilcoxon rank sum test. In addition, considering the multinomial distribution of the grading system (0-2, 3-4, 5-8 points), the cumulative or ordinal logistic model of the changes in the grading system after 12 weeks compared to baseline.

Secondary efficacy variable 2: Pap Smear Test

The reading standard is based **on the 2001 Bethesda System for Reporting Cervical Cytologic Diagnoses**. The results of the study were divided into 6 stages: Negative, ASC-US, ASC-H, LSIL, HSIL, and Invasive cancer (Cervical carcinoma). Considering the multinomial distribution, And the cumulative or ordinal logistic model is used to analyze changes in the classification stage 3 months after the baseline.

Secondary efficacy variable 3: HPV DNA Chip Test

The HPV DNA Chip Test is a test to determine the type of virus infection. It is classified as positive or negative according to the test result. GEE (Generalized Estimating Equation) or Generalized Linear Mixed Model is considered to determine time-dependent changes, group-to-group differences, and time-to-group interactions for baseline versus measured clearance.

Secondary efficacy variable 4: HPV HC Ⅱ assay

GEE (Generalized Estimating Equation) or Generalized Linear Mixed Model is considered to determine time-dependent changes, group-to-group differences, and time-to-group interactions for baseline versus measured clearance.

Secondary efficacy variable 5: NK cell activity

To compare the results of NK cell activity measured at 4 weeks, 8 weeks, and 12 weeks versus baseline (0 week), the mean difference between the baseline and 12-week NK cell levels was calculated as t - Black or Wilcoxon rank sum test.

Secondary efficacy variable 6: MHC class II CD8, CD56 population

GEE (Generalized Estimating Equation) or Generalized Linear Mixed Model is considered to determine time-dependent changes, group-to-group differences, and time-to-group interactions for baseline versus measured clearance.

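### The NK cell activity endpoint is declared at weeks 4, 8 and 12, but the only test specified is on the baseline-to-week-12 change, with no baseline term and with LOCF

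*Protocol*

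**What the plan says.** - **Endpoint.** Section 15.1.2 lists it as "Comparison of results of NK cell activity at 4, 8 and 12 weeks after drug administration compared to baseline (0 week) before drug administration".
- **Sampling.** Section 15.2.2 schedules the blood draws: "Blood is collected from visit 2 and visit 3, visit 4, visit 5". In the flow chart of section 12.1 these visits are weeks 0, 4, 8 and 12.
- **Test.** The NK paragraph of section 15.3.5 begins "To compare the results of NK cell activity measured at 4 weeks, 8 weeks, and 12 weeks versus baseline (0 week" and ends "the mean difference between the baseline and 12-week NK cell levels was calculated as t - Black or Wilcoxon rank sum test". The garbled test name reads as a mistranslation of t-test. The statistical analysis row of the Protocol Outline has the same wording.
- **Companion immune endpoint.** For CD8/CD56 at the same visits, section 15.3.5 says "GEE (Generalized Estimating Equation) or Generalized Linear Mixed Model is considered to determine time-dependent changes, group-to-group differences, and time-to-group interactions".
- **Missing data.** Section 15.3.3 says "LOCF (Last Observed Carried Forward) method is applied to replace missing values". It sets this rule against the one for safety parameters, which are not imputed, so it covers the efficacy variables.
- **Timing.** Section 12.2.15 says "Observe for 8 weeks after completion of the Investigational Product from visit 2 (0 weeks) to visit 3 (4 weeks ± 5 days". Week 12 is therefore 8 weeks after the end of dosing.

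**The concern.** The endpoint has three post-baseline time points and the specified test uses one. Two of the three scheduled draws, including the one at the end of dosing, have no specified comparison between arms. The NK result bears on the mechanism: section 11.1.1 chose the dose on NK activity seen after 5 days of dosing, and the earlier 8-week study in section 6.4 examined NK change at weeks 4 and 8. If the arms differ at week 4 but not at week 12, or the reverse, the protocol does not say which comparison counts.

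Two features of the named test add to this. It compares raw changes, which is valid under randomisation but less precise than a baseline-adjusted comparison. And LOCF lets a week-4 or week-8 value stand as a week-12 value, so the one specified contrast would mix time points. A difference present only around dosing could then appear as a difference 8 weeks later.

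**Working it through.** **Stated figures.** The protocol gives no sample size, standard deviation or power for NK activity. Section 9.3.1 gives 80 evaluable per group and 20% dropout, and 80 / (1 − 0.20) = 100 reproduces its enrolment figure. Both inputs are borrowed below. Everything else is assumed.

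**1. Text side by side.**

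| | Week 4 | Week 8 | Week 12 |
|---|---|---|---|
| NK blood drawn (12.1, 15.2.2) | yes | yes | yes |
| NK endpoint declared (15.1.2) | yes | yes | yes |
| NK aim stated (15.3.5, first half of sentence) | yes | yes | yes |
| NK test named (15.3.5, second half of sentence) | no | no | yes |
| Time-by-group model considered for CD8/CD56 (15.3.5) | yes | yes | yes |

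The mismatch lies between the third and fourth rows, inside one sentence.

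**2. Baseline adjustment.** Let the variance be s² at both baseline and week 12, with correlation rho.

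- Variance of the change: 2s²(1 − rho).
- Variance after adjustment for baseline: s²(1 − rho²).
- Ratio: (1 + rho)/2, which is 0.65, 0.75 and 0.85 at rho 0.3, 0.5 and 0.7. The variance falls by 35%, 25% and 15%.

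The smallest detectable difference at 80 per group, two-sided 5% and 80% power is (1.960 + 0.842) × √(2/80) × SD = 0.443 × SD. In units of s:

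| rho | Change score | Baseline-adjusted |
|---|---|---|
| 0.3 | 0.443 × √1.4 = 0.52 | 0.443 × √0.91 = 0.42 |
| 0.5 | 0.443 × √1.0 = 0.44 | 0.443 × √0.75 = 0.38 |
| 0.7 | 0.443 × √0.6 = 0.34 | 0.443 × √0.51 = 0.32 |

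**3. LOCF.** Let E be the week-4 effect, d the true week-12 effect, and f the share of patients in each arm whose week-4 value is carried forward. The LOCF contrast is (1 − f)d + fE, so the bias is f(E − d).

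- With f = 0.2 and d = 0, the bias is 0.2E. For E = 0.5 SD, a true effect of 0 is estimated as 0.10 SD.
- With f = 0.2 and d = 0.25 SD, the estimate is 0.8 × 0.25 + 0.2 × 0.5 = 0.30 SD.

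For d between 0 and E, 0.2E is the upper limit. It requires every one of the 20% to have week 4 as the last value. If the effect fades steadily, a patient lost before week 4 (baseline carried, change zero) or after week 8 (week-8 value carried) contributes less.

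**4. Relying on week 12 alone.** Take a week-4 effect of 0.5 SD, rho 0.5 and 80 per group. A change-score test at week 4 would have power 0.89. The planned week-12 test would have power 0.66, 0.35 or 0.12 if 75%, 50% or 25% of the effect remained. The protocol supplies no retention figure, so this shows sensitivity and predicts nothing.

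**5. Why not three separate tests.** Three 5% tests would have a familywise error of up to 1 − 0.95³ = 14.3% if independent. One contrast should therefore stay named.

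**The case against.** - **The SAP may add the missing tests.** Visit-wise comparisons and model form for a secondary endpoint are often left to it. The sentence does state the three-visit aim and does not exclude weeks 4 and 8, and the text is visibly translated. A reader might infer that the end-of-treatment effect will never be tested; the protocol does not support that. What stands is that it fixes one test, and that test does not match its own endpoint.
- **Adjustment is not ruled out.** Section 15.3.1 mentions covariance-type models for prognostic factors, including baseline laboratory values. That is true, but the sentence is generic and incomplete, refers to the methods of 15.3.4 and 15.3.6, and does not name NK. An unadjusted change score remains unbiased under randomisation, so this part is about efficiency. The variance ratio assumes equal variances and does not describe the Wilcoxon option.
- **Fading after dosing is not documented.** Neither section 6.4 nor section 11.1.1 gives off-treatment decay, and week 12 coincides with the primary histology, which is a sound reason to keep it as the main contrast. This stands.
- **LOCF is protocol-wide and 0.2E is an extreme case.** Both are correct, and the figure is given only as an upper limit.
- **The CD8/CD56 model is only to be considered.** Also correct; it shows that the protocol contemplates this model class for the same visits, no more.

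**Conclusion.** The point holds as a mismatch between the declared NK endpoint and the only test specified for it. No test is specified at weeks 4 or 8, the named test carries no baseline term, and LOCF would put earlier values into the week-12 contrast.

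The size depends on quantities that the protocol does not give. The 35%, 25% and 15% variance reductions rest on assumed correlations and equal variances. The LOCF figure of about 0.2E rests on 20% dropout, all with week 4 as the last value, and a true week-12 effect of zero. It would be tempting to conclude that the NK effect will have gone by week 12, or that LOCF will create a false one; the document supports neither.

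NK activity is one of six secondary variables in a trial that section 9.3.2 calls exploratory. The primary conclusion rests on histologic regression and is unaffected. The change should be made because it is cheap and removes an ambiguity, not because the trial depends on it.

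**What to change.** Rewrite the NK paragraph in section 15.3.5 and in the Protocol Outline:

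- Use one repeated-measures model with NK activity at weeks 4, 8 and 12 as outcomes, and with arm, visit, arm-by-visit, baseline NK activity and site as terms. Site is included because section 12.2.10 allocates randomisation blocks by institution.
- Fit it to observed data, and exempt NK activity from the LOCF rule in section 15.3.3.
- Keep week 12 as the named contrast, and report weeks 4 and 8 from the same model as supportive.

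Optionally, add a baseline-adjusted comparison of the Reid score. Section 15.3.5 now says that the "difference of the scores after 12 weeks will be confirmed through the t-test or the Wilcoxon rank sum test". Adjustment there is an efficiency gain alongside the ordinal model already planned, not a correction.

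The cost is wording and programming. All the samples are already scheduled, and the model extends a class that the protocol already names for CD8/CD56.

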#### 15.3.6 Analysis on safety evaluation variables

All safety data, including all adverse events collected from patients, clinical laboratory test results, 12-lead ECG, and vital signs (blood pressure and pulse rate) are performed

#### 1) Adverse events

Summarize the adverse events observed following administration of the investigational product. The number of cases and the number of patients who experienced an adverse reaction, abnormal drug response, SAE, death, adverse events n that caused discontinuation of clinical trial, and / or "other significant adverse events (OAE) do. The number of subjects who received each of the abnormal responses was also summarized by body-organ system (SOC), recommended language, and maximum severity for each treatment group. In addition to the summary statistics, the incidence or incidence of adverse events in the group are analyzed using Chi-squared test, Fisher's Exact test, or Poisson test.

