**Protocol Outline**

| Study Title | A multi-center, randomized, double blind, placebo control, parallel design, phase 2b trial to evaluate the efficacy and safety of PGA (Poly-gamma-glutamic Acid) for the fertile women with Cervical Intraepithelial Neoplasia(CIN I) |
| --- | --- |
| Study Phase | Ⅱb |
| Study design | Randomized, Double-blind, Placebo-controlled, Parallel-group |
| Investigators/ Site Name | [name], PhD / The Catholic University of Korea Seoul St. Mary's Hospital  [name], PhD / Korea University Guro Hospital  [name], PhD/ Cheil General Hospital and Women’s Healthcare Center  [name], PhD/ Keimyung University Dongsan Medical Center  [name], PhD/ CHA Gangnam Medical Center, CHA University  [name], PhD/ Gangseo MizMedi Hospital |
| Sponsor | BioLeaders Corporation |
| Purpose | This study is to compare the regression rate of Cervical Intraepithelial Neoplasia (CIN1) between the treatment group and the control group. |
| Investigational Product | - Experimental: Poly-gamma-glutamic acid 1,500 mg  - Comparator: Placebo  - Dosage schedule: 1,500 mg in 100mL po q.d. before bedtime for 4 weeks (28 days) |
| Indication | Women aged 20-49 years with HPV positive CIN 1 |
| Inclusion Criteria | 1. Fertile female aged between 20 and 49  2. Patients who are diagnosed as Cervical intraepithelial neoplasia 1 (CIN1)  3. Patients who are infected with HPV (Human Papilloma Virus) positive (+)  4. White Blood Cell Count(WBC) over 4 10^3^/ul, Hemoglobin above over 9.0g/dL Platelet over 150 10^3^/uL and ANC (Absolute Neutrophil Count) over 1,500 10^6^/L  5. AST (Aspartate Aminotransferase) no less than 4 times higher than normal ALT (Alanine Aminotransferase) no less than 4 times higher than normal  6. Normal for EKG (Electrocardiography) and no active disease detected trough chest X-ray  7. Be informed of the nature of the study and will give written informed consent |

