### 9.3 Sample size

#### 9.3.1 Sample size

##### - Total 200 patients (PGA Group 100 patients, Placebo Group 100patients)

Based on published literature, we assumed that 31% of the cases of CIN 1 would resolve spontaneously, and a clinically significant difference was estimated at 20%. 80 patients per group.

| Group | Dose | Patient | Expected response Rate | Expected response patient | Duration of treatment/Observation |
| --- | --- | --- | --- | --- | --- |
| Placebo | - | 80 | 31% | 24.8 | administered once daily for 4 weeks /  observation for 8 weeks |
| PGA | 1,500mg/day | 80 | 51% | 40.8 |  |
| Total | - | 160 |  |  |  |

Cervical intraepithelial neoplasia (CIN I) can act as a precursor to invasive cervical cancer and is the most common significant gynecologic disease in women of reproductive age. study, we investigated clinical efficacy and immune response of oral administration of γ-PGA from women with cervical intraepithelial neoplasia 1 (CIN 1) in phase 2b study

H_0_ : p_1_≦p2 vs. H_1_ : p_1_>p_2_

p_1_ : Response rate of treatment, p_2_: Response rate of Control

Expected response rate: PGA Group: 81%, Control Group: 51%

significance level : 0.05, statistical power : 80%, one-sided test

The Sample size is total 160 patients, 80 patients per group when the Single stage method.

If 20% drop out is considered, the sample is total 200 patients, 100 patients per group

The sample size is according to the Two stage optimal design (Jung(2008)) Method is shown in the following table.

[Jung(2008) Two-stage]

| Stage | Patient | Difference between two groups (Treatment patient-Control patient) | 제 significance level, statistical power |
| --- | --- | --- | --- |
| 1  2 | 43  80(43+37) | +2  +11 | 0.461, 0.800 |

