###### Confirm medication compliance of Investigational Produc

The study patients will return the empty containers with the Investigational Product taken at Visit 2 (0weeks), the unused medicines, and the recorded medicines daily record, and the research coordinator will return the quantity of medicines prescribed at Visit 2 Determine the quantity of Investigational Product taken by the subject of the clinical trial and record the adherence compliance on the case report sheet as follows. The medicinal compliance of the Investigational Product is considered to be "compliant" if it is> 80%.

Compliance (%) = Number of Investigational Products Taken / Number of Investigational Products Taken X 100

- - 1. **Assessing Adverse Events**

Adverse events are closely monitored from the time of administration to the end of the clinical trial. In the event of an adverse event, the date and time of the adverse event, the extent and consequences of the adverse reaction, the measures taken in relation to the Investigational Product, the causal relationship with the Investigational Product, the name of the suspected drug other than the test drug, and details of the contents are recorded. After the visit, the adverse reaction should be immediately reported to the researcher, the clinical trial patient should be trained so that the patient can be admitted to the clinic, and the researcher should be contacted. The evaluation, recording and treatment of detailed adverse events is in accordance with section 16.3.

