###### 15.3 Statistical analysis method

**15.3.1 General principles of analysis**

The purpose of this study was to investigate the effect of oral administration of polygamma glutamic acid (γ-PGA) on the cervical intraepithelial dysplasia (CIN) Phase II clinical studies to confirm. All data obtained in this study are summed up as mean ± standard deviation for continuous data and categorical data for the number of subjects (fraction), and various summary statistics are presented when necessary. If it is necessary to provide an interval estimate, a 95% confidence interval shall be provided.

In the statistical analysis of this data, the first validity criterion, the healing rate, is to be carried out by a one-sided test at a significance level of 5% based on the method of Jung (2008) in the appropriate validity analysis group defined in 15.2. In the analysis other than the primary efficacy evaluation item, the two-sided test is performed at the significance level of 5%. In addition to the efficacy evaluation methods and safety evaluation methods described in 15.3.4 and 15.3.6, when prognostic factors contributing to the outcome variables such as age, perinatal risk, baseline laboratory values, (Eg, logistic model, ANOCOVA, generalized linear model, etc.).

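### Adverse event incidence is tested on all events after administration, on the plain reading 12 weeks, with no comparison for the 4 weeks of dosing; adding one is cheap and keeps the 12-week test

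*Protocol*

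**What the plan says.** **Dosing.** The Section 9.3.1 table has the product "administered once daily for 4 weeks"; the Protocol Outline gives 28 days. Section 12.2.15 continues: "Observe for 8 weeks after completion of the Investigational Product".

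**Collection.** Under Assessing Adverse Events in Section 12.2: "Adverse events are closely monitored from the time of administration to the end of the clinical trial". The schedule in Section 12.1 checks adverse events at Visits 3, 4 and 5 (weeks 4, 8 and 12). Section 16.3 has the start and end date of each event recorded.

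**Analysis.** The adverse event item of Section 15.3.6, with the same text in the Outline, says "Summarize the adverse events observed following administration of the investigational product". It then asks for counts by type of event and summaries by organ class, term and maximum severity for each group. On testing it says "adverse events in the group are analyzed using Chi-squared test, Fisher's Exact test, or Poisson test". Section 15.3.1 sets the level: "In the analysis other than the primary efficacy evaluation item, the two-sided test is performed at the significance level of 5" per cent.

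The adverse event item names no period and no split by period. The next item of the same section does compare ECG abnormalities by time point.

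**The concern.** Two thirds of the collection period (8 of 12 weeks) is off drug. For harm tied to taking the product, those weeks add the same expected background events to both groups. The difference between groups shrinks and the variance grows. The only between-group comparison that the text fixes is therefore not the one best suited to a simple question: is the product tolerated while it is being taken? An excess during dosing would be less likely to show in the stated tests, even though the onset dates needed to isolate it are collected anyway.

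**Working it through.** **The plan's own figure.** The protocol gives no power or sample size for safety. Its only sizing is for efficacy: 80 per group at a stated power of 0.800, then "If 20% drop out is considered, the sample is total 200 patients, 100 patients per group". Exact two-stage binomial calculation from its cut-offs (+2 of 43, +11 of 80) gives power 0.805, and 80/(1 − 0.20) = 100. So 100 per group is the number randomized.

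**Inputs from the protocol.** Dosing 4 weeks; follow-up 12 weeks; 100 per group; two-sided 5%.

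**Inputs that must be assumed.** Background event rate and size of harm. Sections 13.1 and 16.2 say only that no significant adverse events were seen before.

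**Model A: constant background hazard, multiplied by HR during dosing only.**

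- h = −ln(1 − I)/12, where I is the 12-week background incidence.
- Dosing window: 1 − exp(−4h) against 1 − exp(−4h·HR).
- 12 weeks: 1 − exp(−12h) against 1 − exp(−h(4·HR + 8)).
- Power = Φ{[d√n − 1.96√(2p̄(1 − p̄))] / √(p₁(1 − p₁) + p₂(1 − p₂))}, where d is the difference and p̄ the mean of the two proportions.

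Worked case, I = 30% and HR = 2: h = 0.3567/12 = 0.0297.

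- Dosing window: 11.2% v 21.2%, d = 0.0995. Power = Φ[(0.995 − 1.021)/0.516] = Φ(−0.05) = 48%.
- 12 weeks: 30.0% v 37.8%, d = 0.0785. Power = Φ[(0.785 − 1.312)/0.667] = Φ(−0.79) = 21%.

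The 12-week difference is the dosing-period difference times exp(−8h) = 0.788, which is the dilution itself.

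| Background over 12 weeks | HR on drug | Power, dosing window | Power, 12 weeks |
|---|---|---|---|
| 20% | 2 | 33% | 16% |
| 30% | 2 | 48% | 21% |
| 30% | 2.5 | 76% | 39% |
| 30% | 3 | 91% | 58% |
| 50% | 2 | 73% | 31% |

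With 80 per group, the 30%, HR 2 case gives 40% and 18%.

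**Model B: background risk b per 4 weeks, added risk a during dosing only.** Dosing window: b v 1 − (1 − b)(1 − a). 12 weeks: 1 − (1 − b)³ v 1 − (1 − b)³(1 − a). The difference falls from (1 − b)a to (1 − b)³a. Same power formula, 100 per group:

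| b | a | Dosing window | 12 weeks | Ratio |
|---|---|---|---|---|
| 1% | 10% | 0.85 | 0.73 | 0.86 |
| 1% | 25% | 1.00 | 1.00 | 1.00 |
| 5% | 10% | 0.62 | 0.34 | 0.55 |
| 5% | 20% | 0.97 | 0.83 | 0.85 |
| 10% | 15% | 0.73 | 0.38 | 0.52 |
| 20% | 20% | 0.72 | 0.31 | 0.43 |
| 30% | 20% | 0.54 | 0.18 | 0.34 |

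Over b from 1% to 30% and a from 10% to 25%, the ratio runs from 0.34 to 1.00. Exact enumeration of the chi-squared test gives nearly the same ratios. A Poisson count model agrees: 0.1 background events per 4 weeks, doubled on drug, gives 0.45 against 0.22.

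**If the excess does not stop with dosing.** In Model A with I = 30% and the hazard doubled for all 12 weeks, the 12-week comparison is 30% v 1 − 0.7² = 51%. Its power is 86%, against 48% for the dosing window. In Model B with b = 5% and 5% added in every 4-week period, power is 0.57 over 12 weeks against 0.25 over 4.

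**The case against.** The case for leaving the text alone has four parts.

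1. **An on-treatment window is often set in the statistical analysis plan, which is not at hand.** The adverse event item never says 12 weeks and does not forbid a split. This stands as a limit on severity. But the protocol does name the event set and the tests, and it ties the tests to all events after administration.

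2. **A reader might infer that 8 weeks of background would hide an on-drug excess altogether.** The documents do not support that. The same item asks for drug reactions, serious events, events causing discontinuation, and tables by organ class, term and severity. Causality grading in Section 16.3 uses timing relative to dosing, and laboratory tests and vital signs are taken at Visit 3. These are summaries rather than tests of the dosing period, but an excess would have places to appear.

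3. **A reader might infer that power is simply halved.** That needs event rates and a size of harm that the protocol does not give. Halving fits moderately common events with moderate harm. With rare events or large effects the loss is small.

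4. **A reader might infer that the 12-week comparison is wrong and should be replaced.** It is a valid randomized comparison. Section 6.3 describes the product as acting through immune activation, and Section 15.1.2 follows immune markers to week 12, so late or lasting effects cannot be ruled out. Moving the test to the dosing period alone would give up power for them.

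What survives is narrower: no dosing-period comparison is stated, and the data for one are already collected.

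**Conclusion.** The point holds as a low-cost improvement, not as an error in the plan. The dosing length, the collection period and the absence of a dosing-period comparison come from the protocol; the 12-week period of the test is the plain reading rather than stated text. If harm is confined to dosing and background events occur at a constant rate, dilution follows by arithmetic. Its size rests on assumed rates: the 12-week comparison keeps between about one third and nearly all of the power of a dosing-period comparison, with 48% falling to 21% as one example. Even there the dosing-period test misses the excess about half the time, so it improves the picture without settling the question. If harm persists or is delayed, the ranking reverses. Neither window is best for both kinds of harm, so both should be reported.

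**What to change.** In the adverse event item of Section 15.3.6 and the matching text in the Outline:

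- Keep the comparison over the full 12 weeks, and state that this is its period.
- Add a between-group comparison of events with onset from first dose to the end of dosing (Visit 3), using the recorded start dates. Use the same window for every woman in the safety set, whether or not she stopped early.
- Show events with onset after Visit 3, to week 12, in a separate table so that delayed effects stay visible.
- Say that these safety comparisons are unadjusted for multiplicity and are read descriptively.

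If the statistical analysis plan already defines such a split, aligning the protocol wording is enough. The cost is a few lines of text, one more table split and one more unadjusted comparison. No new data, visits or patients are needed.
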